### Interim analyses and stopping rules

The Data Management Committee (DMC) will be established for the study. The Data Management Committee will be an independent group separate from the sponsor, with no competing interests [41]. The Committee members will represent different disciplines and areas: nurse association, health services, statistics, and ethics, for example. The role of the Committee will be to ensure the quality of the data, data collection, data privacy, safety of the intervention, incorporation of participant feedback, and data analysis and to provide further recommendations for the study [41]. A Trial Steering Committee (TSC) will be established. The role of the TSC will be to oversee the study, make decisions based on the recommendations of the Data Monitoring Committee (DMC), endorse actions, and provide advice on daily operations. Its members will include both independent experts and members of the research team [42].

In addition, day-to-day coordination has already been established to manage the operational aspects necessary to ensure the smooth execution of the research project and to maintain responsibilities that will help keep the study on track and aligned with its objectives. This includes weekly meetings with research team members, as well as planning and scheduling (e.g., recruitment, data collection, data management, and analysis), team communication (e.g., organising meetings, providing updates, ensuring systematic information flow, and ad-hoc communication), recruitment and data management (e.g., data privacy, storage, and management according to protocol), ethics, resource management, and progress monitoring (milestones, delays, achievements), as well as reporting and documentation, staff training, and problem-solving.

The trial conduct will be monitored internally by the research team, with meetings scheduled twice a month to ensure adherence to the protocol and ethical standards. Additionally, the DMC oversees trial conduct, maintaining data integrity throughout the trial period (meeting scheduled twice a year).

Only study investigators, i.e. the Principal Investigator (MV), researcher (MS), and statistician (MY) will have access to the data. No interim analysis will be conducted. The results of the baseline data analysis will be shared and discussed with the DMC. If any significant external factors arise, such as nursing strikes, major organisational changes that alter the unit leaders’ roles, or severe resource shortages within the participating organisations that threaten the study’s implementation or participant recruitment, the trial may be terminated. The final decision to stop the trial will be made by the TSC based on the recommendations of the DMC.

Code breaks will occur only in exceptional circumstances, for example, if during the analysis, the statisticians detect any harm in the data scores. However, this will be done only after discussions with the TSC and based on recommendations of the DCM.

No adverse effects are anticipated due to the educational nature of the intervention. At the end of the intervention, all participants will be systematically asked about any perceived burden or harm caused by the intervention. If participants have perceived (ad-hoc or based on systematic assessment) any unintended effects or burden during or at the end of the intervention, they will be advised to seek care and support from the organisation’s occupational health services. All reports will be reviewed by the principal investigator and discussed during DMC meetings.

The specific criteria for stopping the study are as follows: [1] a significant decline in participant engagement or attendance (e.g. less than 20% course participation) may indicate that the intervention is no longer effective or relevant; [2] consistent negative feedback from participants regarding the content, format, or delivery of the intervention may warrant its cessation; [3] the educational intervention may not be financially sustainable due to unforeseen events (e.g. a catastrophe or staff strike); [4] changes in organisational policies, on-the-job training standards, or regulations may necessitate cessation; and [5] the introduction of a similar compulsory educational initiative or program that supersedes the current intervention may lead to its discontinuation.

We have confirmed that the study organisations are not currently conducting or planning any other leadership courses offered by the employer during the 7-month trial. If similar courses are organised, leaders in the intervention and control groups cannot be restricted from attending other leadership courses. Information about staff members’ participation in any on-the-job training will be collected to identify any potential source of contamination or any factors influencing the effectiveness of the intervention. If the study participant has joined any other leadership course, she/he is able to do so, and it will be reported and considered during the data analysis.

### Data management and statistical analysis

All data will be processed in accordance with the European Union’s (EU) General Data Protection Regulation [43]. The data will not be shared with anyone outside the research team or transferred to another register or to another personal data processor. The quality of the data will be ensured through the use of double data entry. The data will be collected with the participants’ informed consent. Electronic informed consent will be obtained using the REDCap tool. Only the Principal Investigator (MV) and the researcher (MS) will have access to the data related to the obtained informed consent digital documents. The participants will have the right to withdraw from the study, to access their personal data, to demand that their data is rectified or deleted, to restrict the processing of personal data, and to lodge a complaint if they believe a violation of applicable data protection laws has taken place [43].

All study-related information in paper format will be stored securely at the research office. All reports, data collection, processing, and administrative forms will be identified only by a coded ID number to maintain participant confidentiality. All records that contain names or other personal identifiers will be archived separately from the study records identified by the code numbers. All databases will be secured with password-protected codes. Any data for monitoring purposes (data monitoring excel) linking participant ID numbers to other identifying information will be stored in a separate, locked file. Baseline and follow-up data collected from the participants will be stored in a secure cloud storage service provided by the IT services of the University of Turku, with access restricted through password protection. The electronic data collected will be managed with REDCap, a secure, web-based software platform used to conduct research studies [40]. Each research personnel member will receive centralised training on the study requirements through a total of 4 h of hands-on training sessions. These sessions will cover topics such as the use of instruments, obtaining informed consent, data collection procedures, safety issues, voluntariness, and the right to withdraw from the study. All team members are trained to perform quality control and anticipate risks. The Principal Investigator (PI) is responsible for planning and overseeing data management and metadata sharing. The researchers will conduct the data collection, processing, analysis, storage, and organisation. Participant retention and upcoming follow-up data collection will be supported with email reminders. Participant retention and follow-up will be monitored using the Moodle learning platform and REDCap.

Data analysis will be carried out on an intent-to-treat (ITT) basis; every effort will be made to collect outcome data from all participants, regardless of whether they completed the intervention. Assumptions of normality of the residuals will be investigated. The characteristics of the units and respondents (staff members) will be summarised with descriptive statistics for each group. The specific metric will be the change between the baseline score and the final score at 7 months. The method of aggregation or the summary statistics will be based on the type of outcomes. Mean score will be used for score measurement such as the EBPQ, self-esteem, self-efficacy, and EBP scales. The Quality of care and Work absence and intention to leave will be summarised using both count and proportions.

All individuals within the cluster will be included in the trial. Possible duplicate measurements will be identified using participant ID codes, email addresses, or monitoring records.

A descriptive summary of the baseline information for both clusters and individuals will be presented first as tables of summary data. For the primary outcome EBPQ, its change from the baseline to the time immediately after the intervention (key time point) will be analysed with mixed effects linear models (respondents nested within units). In such models, the mean difference in EBPQ scores from baseline to the key point of intervention will be compared between the intervention and passive control groups, with random effects among unit leaders being estimated and characteristics of participants and units being adjusted. The changes in the subscales of the EBPQ will be analysed using multivariate mixed effects models in which simultaneous models for the three subscales are analysed jointly to overcome the inter-subscale correlation that might lead to multi-comparison bias [44]. Multiple imputations for the EBPQ and its subscales will be considered if data is missing at random. The same models will be used for the secondary outcomes, such as scores on the RSE, GSE, EBP and other continuous respondent-level outcomes. For unit-level outcomes at the key point, such as death, number of reported complaints, and number of staff’s sick days, generalised linear models will be used to compare the differences between the two groups with adjustment for unit characteristics.

Sensitivity analyses will be conducted for units in which participation in online training is low to evaluate whether intervention fidelity has any effect on the results of the primary outcome. Results will be expressed using rate ratios, odds ratios, or least-squares mean differences with corresponding 95% CIs, depending on the type of outcome.

As our study will be a cluster randomised controlled trial, its analysis requires special consideration of the correlations within and between the clusters. First, in the sample size calculation, a clustering effect was assumed and accounted for as the ICC coefficient. Second, for the primary analysis, the intracluster (intraclass) correlation coefficient (ICC) will be reported as the proportion of the total variance of the outcome that can be explained by the variation between clusters [14]. For data analysis, the mixed effects model or two-level multilevel models that consider clustering effects will be used. In the model analysis, the variation in the outcomes among clusters will be estimated and tested for significance. Third, the overall efficacy of the outcomes will be estimated after considering the clustering effects.

In addition, covariate analysis will be conducted to control for potential confounding factors in statistical modelling. Participants’ age (novice, senior) and gender (male, female, other), status (unit leader, other staff member) and the engagement of course tasks (number of returned tasks by each participant in the intervention group) will be included in the analysis.

Statistical analyses will be performed with the SAS System for Windows, version 9.4 (SAS Institute Inc) and SPSS, versions 25.0 to 27.0 (IBM Corp). Because no adjustments for multiplicity of testing will be made, only 95% CIs will be reported for the secondary outcomes.

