### Sample size

A previous study indicated a 6-point increase in the EBPQ outcome from baseline to a key time point in the intervention group and a 5-point decrease over time in the control group [35]. We assume there will be a 10-point difference in the change of the primary outcome over time between the two groups and an estimated standard deviation of 20 [36]. With a power of 80%, a 5% type I error with a two-sided test, an inter-class correlation (ICC) of 0.03, and an average unit size of 25 with a variation of 1, the estimated sample at the cluster level is 12, 6 in each treatment arm. This would mean a total of 300 participants, 150 in each arm. As in many other trials, we anticipate challenges in recruitment and adherence due to the limited time and resources of nurse staff, trial-specific issues, communication difficulties, inadequate research experience and training, and a lack of incentives [37]. We assume that if 58% of participants complete the post-intervention assessment after the online training [38], the number of staff to be recruited for the study should be 517. Generally, if the average response rate for the baseline is 42% [39], we should aim to approach at least 1,238 nursing staff. The potential number of participants needed for this study is feasible, as the data will be collected in the wide region in south Finland. The power calculation was made using PASS 15 software for a cluster randomised design.

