### Randomisation

Randomisation in this study will be conducted at the unit level (cluster), not at the hospital level. Units participating in the study will be randomly assigned (1:1) to one of two parallel groups: either the evidence-based leadership training group or the passive control group. This will be done using a computer-generated randomisation list developed by an independent trial statistician. To ensure balance between the study groups, units will be stratified based on the number of staff members in each unit as follows: (I) small units and (II) large units, determined by the median number of staff members in each unit. The randomisation will be generated using SAS software, Version 9.4 of the SAS System for Windows (SAS Institute Inc., Cary, NC, USA).

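### The primary model analyses EBPQ change without naming baseline EBPQ as a covariate, which gives up precision and over-corrects chance baseline imbalance between 6 and 6 units

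*Protocol article*

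**What the plan says.** The Protocol article, Data management and statistical analysis, fixes the outcome metric: "The specific metric will be the change between the baseline score and the final score at 7 months". For the EBPQ, "its change from the baseline to the time immediately after the intervention (key time point) will be analysed with mixed effects linear models", with respondents nested in units and with adjustment for characteristics of participants and units. The same section later names age, gender, status (leader or other staff) and number of returned course tasks as covariates, and extends the same models to RSE, GSE and the other continuous respondent-level outcomes.

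Baseline EBPQ is not in that list. Nor is it among the participant characteristics under Characteristics of the units and participants, which are age, gender, degrees, position and length of experience. The sections on Recruitment and on Blinding and masking place the baseline survey before randomisation.

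Under Randomisation, "units will be stratified based on the number of staff members in each unit as follows: (I) small units and (II) large units", split at the median. The analysis section does not name this stratum as a model term. Total number of staff is, however, one of the collected unit characteristics.

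**The concern.** Modelling change without baseline as a covariate assumes that each point of baseline difference carries through to month 7 in full. When the correlation between the two measurements is below 1 and the SDs are similar, only part of it does. Two things follow.

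- **Precision.** The treatment estimate has a larger variance than one from a model that estimates the baseline slope.
- **Chance imbalance.** Subtracting the whole baseline difference corrects too much. The arm that happens to start higher tends to show a smaller gain, for reasons unrelated to the course.

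With 6 units per arm, some chance imbalance in baseline EBPQ is to be expected. The covariate that deals with both problems is already planned to be collected.

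**Working it through.** **Inputs from Sample size.** "With a power of 80%, a 5% type I error with a two-sided test"; a "10-point difference in the change of the primary outcome over time between the two groups"; "an estimated standard deviation of 20"; "an inter-class correlation (ICC) of 0.03"; "an average unit size of 25 with a variation of 1"; 6 units per arm. The section does not say whether 20 is the SD of the change or of the score.

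**Assumed.** The baseline-to-follow-up correlation r is not in the document, so a range is shown. The formulas below also assume equal SDs at both times and the same r within and between units.

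**Step 1: reproduce the plan's figure.**
- Design effect: 1 + (25 − 1) × 0.03 = 1.72.
- Standard error with 6 units of 25 per arm: 20 × √(2 × 1.72 / 150) = 3.03. The non-centrality is 10 / 3.03 = 3.30.
- A two-sided t-test on 2 × 6 − 2 = 10 df gives power 84.4%. Five units per arm (8 df) give 75.2%.
- Six is therefore the smallest number per arm that reaches 80%, which agrees with the stated 12 units and 300 participants.
- Reading the variation of 1 as an SD of unit size (CV 0.04) still gives 84.4%.

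**Step 2: relative precision.** With score SD s:
- Var(change) = 2s²(1 − r)
- Var(ANCOVA residual) = s²(1 − r²)
- Ratio = (1 + r)/2, which is 0.65, 0.75, 0.85 and 0.90 at r = 0.3, 0.5, 0.7 and 0.8.

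**Step 3: power with 6 units per arm, 10 df.**

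| r | SD 20 is of change: change score | SD 20 is of change: ANCOVA | SD 20 is of score: change score | SD 20 is of score: ANCOVA |
|---|---|---|---|---|
| 0.3 | 84.4% | 95.7% | 71.1% (SD 23.7) | 87.6% (SD 19.1) |
| 0.4 | 84.4% | 94.4% | 77.5% (SD 21.9) | 90.0% (SD 18.3) |
| 0.5 | 84.4% | 92.9% | 84.4% (SD 20.0) | 92.9% (SD 17.3) |
| 0.7 | 84.4% | 89.6% | 96.9% (SD 15.5) | 98.6% (SD 14.3) |

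Under the score-SD reading, change-score power crosses 80% at r of about 0.44. The baseline-adjusted model does not fall below 84.4% for any r from 0 upwards, because its residual SD cannot exceed 20.

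**Step 4: chance imbalance.** Take the score SD as 20, the baseline ICC as 0.03 and 150 per arm.
- SE of the baseline difference between arms: 20 × √(2 × 1.72 / 150) = 3.0 points, so a 95% range of about ±5.9.
- Conditional error of the change-score estimate: −(1 − r) × imbalance.
- At r = 0.5, a 3-point imbalance gives −1.5 points and a 5.9-point imbalance about −3.0 points, against a planned effect of 10.

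**Step 5: the stratum term.** It uses one between-unit degree of freedom (10 to 9). If it explains nothing, 84.4% becomes 83.5%. Its gain cannot be computed, because the document gives no stratum effect.

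**The case against.** The plan is coherent as it stands. The endpoint, the sample size and the analysis all refer to change, and the stated size reproduces and exceeds 80% if 20 is the SD of change, which is a natural reading of the sentence it stands in. The change-score estimate is unbiased over repeated randomisation. The size of the gain depends on a correlation that the document does not give. The covariate list is not said to be exhaustive, and a fuller analysis plan may add terms. All of this stands, and it keeps the point at the level of an improvement. It does not remove it: the article fixes the change score as the metric and names covariates without baseline EBPQ, and for any r below 1 the alternative is more precise under the stated assumptions.

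A reader might infer three stronger claims that the document does not support.

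- **That baseline imbalance goes uncorrected.** A change score subtracts all of it; the fault is over-correction.
- **That the analysis is unadjusted.** Participant and unit characteristics are adjusted for.
- **That the randomisation stratum is left out.** It is only unnamed. Total staff is a collected unit characteristic, so the general adjustment for unit characteristics may already cover it.

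**Conclusion.** The point holds as a loss of efficiency plus a conditional bias, and not as an error in the plan. Without baseline EBPQ as a covariate, the change-score variance is larger than it need be by a factor of 2/(1 + r): about 1.54, 1.33 and 1.18 at r = 0.3, 0.5 and 0.7. Whether this threatens the power target depends on what the SD of 20 describes. If it is the SD of change, the target is met either way and adjustment adds margin. If it is the SD of the score, the target is missed for r under about 0.44 unless baseline is in the model. Conditional on a typical 3-point imbalance, the estimate is off by about 1.5 points at r = 0.5. These sizes rest on an assumed r, equal SDs and a common correlation within and between units. On the stratum, the document supports no more than a request to name it.

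**What to change.** State the primary model as month-7 EBPQ on arm, baseline EBPQ, age, gender and status, with a random intercept for unit. Using change as the dependent variable gives the same treatment effect once baseline is in the model, so the change metric can be kept. Use the same form for RSE, GSE and ILS, each with its own baseline. Name the small/large randomisation stratum explicitly as the unit-size term.

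The cost is a sentence of analysis wording before the data are released, with no new data collection. The stratum costs at most one between-unit degree of freedom. With baseline and stratum both in the model, and 20 taken as the SD of change, power at r = 0.5 is still 92.3% on 9 df.

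### Joint modelling of the three EBPQ subscales is credited with removing multiple-comparison bias, which it does not do by itself; the primary EBPQ test is unaffected

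*Protocol article*

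**What the plan says.** Under Outcomes, the EBPQ is the primary outcome. Its three subscales (knowledge/skills, attitudes, evidence-based practice) are described under that same heading and are not listed among the secondary outcomes.

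Under Data management and statistical analysis, the change in the EBPQ is analysed in a mixed linear model. The article then adds: "The changes in the subscales of the EBPQ will be analysed using multivariate mixed effects models". The reason given is that "simultaneous models for the three subscales are analysed jointly to overcome the inter-subscale correlation that might lead to multi-comparison bias". It describes no global test, ordering, alpha split or adjusted p-value for the subscales.

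The same section says that results will be given, depending on outcome type, as ratios or as "least-squares mean differences with corresponding 95% CIs". It closes with: "Because no adjustments for multiplicity of testing will be made, only 95% CIs will be reported for the secondary outcomes".

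The only significance level in the article is in Sample size: "With a power of 80%, a 5% type I error with a two-sided test, an inter-class correlation (ICC) of 0.03". It belongs to a single EBPQ comparison, a "10-point difference in the change of the primary outcome over time between the two groups and an estimated standard deviation of 20".

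**The concern.** The rationale treats correlation between subscales as the cause of the multiplicity problem and joint modelling as its cure. Neither is right. Three contrasts create the problem, and each has its own error rate whatever the correlation. A joint model supplies the covariance matrix that a multiplicity procedure could use, but some further step has to use it, and the article names none.

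The subscales also fall into a gap. The plan's answer to the absence of adjustment is interval-only reporting, and that rule is worded for the secondary outcomes. The subscales are described under the primary outcome, so the only protection stated for them is the mistaken one.

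What is at stake is interpretation. Suppose the whole EBPQ score shows no effect but one subscale interval excludes zero. A report could then cite the analysis section as evidence that multiplicity had been handled. The third subscale makes this easier, because it carries the same name as the primary outcome.

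**Working it through.** **1. The plan's own figure.** The inputs are in Sample size: difference 10, SD 20, two-sided alpha 0.05, power 80%, ICC 0.03, and "an average unit size of 25 with a variation of 1".

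- Per arm without clustering: n = 2 × (1.96 + 0.84)² × 20² / 10² = 62.7, so 63.
- Design effect: 1 + (25 − 1) × 0.03 = 1.72. Reading the variation as an SD of 1 (coefficient of variation 1/25 = 0.04) gives 1.7212, which makes no practical difference.
- 63 × 1.72 = 108.4 per arm, and 108.4 / 25 = 4.33 clusters per arm.
- With a noncentral t on 2(K − 1) degrees of freedom, power is 75.2% for K = 5 and 84.4% for K = 6. Six per arm, 12 in all, is the smallest number that reaches 80%.

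The stated 12 clusters and 300 participants reproduce. The 5% in that calculation is spent on one EBPQ contrast. The article states no family-wise rate for the subscales, so there is no figure to reproduce for them.

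**2. Inputs for the subscales.**

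- Number of contrasts: 3 (Outcomes).
- Level per contrast: two-sided 5%. This is inferred from the only stated alpha and from unadjusted 95% intervals; it is not stated for the subscales.
- Correlation r between the three test statistics: not given, so a range from 0 to 0.9 is assumed.
- All three null hypotheses are true.

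**3. Family-wise error.** With independent statistics, 1 − (1 − 0.05)³ = 1 − 0.857375 = 0.1426. With common correlation r, the quantity is P(max |Zⱼ| > 1.96) for three standard normal statistics, here from 4 million simulated draws:

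| r | At least one false positive |
|---|---|
| 0 | 14.3% |
| 0.3 | 13.6% |
| 0.5 | 12.5% |
| 0.7 | 10.9% |
| 0.8 | 9.8% |
| 0.9 | 8.4% |

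The rate falls as r rises. Correlation therefore reduces the family-wise error.

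**4. Small-sample check.** Three t tests on cluster-level values, 6 against 6 with 10 degrees of freedom, were simulated 200,000 times per setting. The family-wise rate was 14.1% (r = 0), 13.7% (0.3), 12.8% (0.5), 12.1% (0.6) and 10.2% (0.8). Each single contrast rejected between 4.9% and 5.1% of the time at every r, so the correlation left the per-contrast error unchanged. This check uses cluster-level t tests; the multivariate mixed model itself was not fitted.

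**5. What an adjustment would do.** Under three true nulls, Holm makes at least one rejection exactly when the smallest p-value is at or below 0.05/3 = 0.0167. With independent statistics the rate is 1 − (1 − 0.0167)³ = 4.9%.

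**The case against.** The strongest reply is that the article never says the subscales are tested one by one at 5%. It has one primary hypothesis and one powered comparison, and it says openly that no multiplicity adjustment is made. Joint analysis is also compatible with a single 3-degree-of-freedom arm test, which would hold 5% for the global null. How a supportive subscale analysis is tested is the kind of detail that an article leaves to a statistical analysis plan. The source cited for the joint model is not at hand either.

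Much of this stands. A reader might infer that the plan fixes three 5% subscale tests with a family-wise error of about 11 to 14%. The document does not support that. The per-subscale level is an inference. The 11 to 14% range needs r between about 0 and 0.7, and its top end needs uncorrelated subscales, contrary to the plan's own premise. A reader might also infer that a subscale may stand in for the whole score, or that the primary test is inflated; nothing in the article says either.

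The reply does not rescue the rationale itself. Leaving a procedure to another document is acceptable, but here the article gives a reason, and the reason is wrong. A global test would be a legitimate use of the joint model, but none is described. Nor does the general admission that nothing is adjusted settle the matter, because its consequence, intervals only, is drawn for the secondary outcomes alone.

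**Conclusion.** The point holds as a correction to the stated rationale and as a gap in how the subscales are to be reported. Joint modelling does not by itself control family-wise error across three subscale contrasts, and correlation is not what creates the multiplicity.

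The size is conditional: roughly 8 to 14% for at least one false-positive subscale, against a nominal 5%. It rests on reading each contrast at two-sided 5%, on all three nulls being true, and on assumed correlations from 0.9 down to 0. The 5% level of the whole-score EBPQ test, the sample size and the primary conclusion are not touched. This is a minor point, worth settling before outcome data are seen because it determines what may be claimed from the subscales.

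**What to change.** In Data management and statistical analysis:

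- Delete the statement that joint modelling deals with multiple comparisons. The joint model can stay, described as a way of estimating the three effects together with their covariance.
- State that the EBPQ total is the only primary test. The sample size and model description already read that way, so this only makes it explicit.
- Choose one rule for the subscales. Either extend the interval-only rule to them, with unadjusted 95% intervals labelled as supportive, or, if subscale p-values are to be claimed, take Holm-adjusted p-values from the planned joint model. Holm is sufficient alone; a global test as an extra gate is not needed.

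The cost is a sentence or two, with no new data, no larger sample and no different model. The one downside is that subscale claims become slightly harder to make.

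### With about 42% of month-7 EBPQ scores expected to be missing, the stated change-score model uses completers only without listing baseline EBPQ as a covariate, and imputation hangs on a condition the data cannot establish

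*Protocol article*

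**What the plan says.** All references are to the protocol article.

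- **Expected loss.** The Sample size section reads "We assume that if 58% of participants complete the post-intervention assessment after the online training", and from this concludes that "the number of staff to be recruited for the study should be 517". The analysis sample is fixed separately: "This would mean a total of 300 participants, 150 in each arm".
- **Planned effect.** The same section assumes "a 10-point difference in the change of the primary outcome over time between the two groups and an estimated standard deviation of 20".
- **Analysis principle.** Data management and statistical analysis states: "Data analysis will be carried out on an intent-to-treat (ITT) basis". It adds that outcomes will be sought from everyone, whether or not they finished the course.
- **Primary model.** The same section sets the metric as the difference between the baseline and 7-month scores. This is analysed with linear mixed models that have respondents nested in units, later described as two-level. The named covariates are age, gender, status (leader or other staff) and course-task engagement. Participant and unit characteristics are also mentioned in general terms. Baseline EBPQ is not listed.
- **Missing data.** The only rule is "Multiple imputations for the EBPQ and its subscales will be considered if data is missing at random".
- **Baseline availability.** Recruitment, and Blinding and masking, both place the baseline survey before randomisation, so baseline EBPQ should exist for nearly all recruited participants.

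**The concern.** A change score does not exist for someone without a month-7 survey. A model with only respondent and unit levels has no occasion level through which a baseline-only respondent could contribute, so following the text gives a completer analysis.

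The imputation sentence does not repair this. Observed data cannot distinguish data missing at random (MAR) from data missing not at random (MNAR), so the condition can never be confirmed. The wording also leaves the decision open until the data are in hand. If MAR is doubted, the text offers nothing except the completer analysis.

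Two kinds of bias are at stake. If response depends on baseline EBPQ differently in the two arms, an unadjusted completer change score is biased even though the data are MAR, and conditioning on baseline would remove that bias. If response depends on the unseen change itself, no MAR method removes the bias, but a sensitivity analysis can show how much it matters. Arm-dependent response is plausible here: allocation is unmasked, the EBPQ is self-reported, and course tasks involve the team in intervention units while control units have no activity.

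**Working it through.** **1. The plan's own figures**

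- Inputs: difference 10, SD 20, ICC 0.03, 25 per unit, 80% power, 5% two-sided.
- Design effect: 1 + (25 − 1) × 0.03 = 1.72.
- Power from a noncentral t on 2(K − 1) degrees of freedom, with cluster-size CV 1/25: 75.2% at K = 5 units per arm and 84.4% at K = 6. This reproduces 12 units and 300 people.
- Recruitment: 300 / 0.58 = 517.2, stated as 517.
- Expected missing: 517 − 300 = 217, and 217 / 517 = 42.0%.

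This 42% is not the other 42% in the section ("if the average response rate for the baseline is 42% [39], we should aim to approach at least 1,238 nursing staff"), which concerns response before enrolment. The power calculation rests on the 300 completers, which agrees with a completers-only analysis.

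**2. Bias of the completer contrast**

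Let g be the completer mean change minus the non-completer mean change in an arm, and p the retention in that arm.

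Bias = (1 − p_I) × g_I − (1 − p_C) × g_C

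The values of g and the unequal retention figures are assumptions.

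| Retention I / C | g_I | g_C | Bias (points) |
|---|---|---|---|
| 0.58 / 0.58 | 10 | 10 | 0 |
| 0.58 / 0.58 | 5 | 0 | 0.42 × 5 = 2.1 |
| 0.58 / 0.58 | 10 | 0 | 0.42 × 10 = 4.2 |
| 0.53 / 0.63 | 10 | 10 | 4.7 − 3.7 = 1.0 |
| 0.48 / 0.68 | 10 | 10 | 5.2 − 3.2 = 2.0 |

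**3. How far a positive result could move**

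- Design SE: 20 × √(2 × 1.72 / 150) = 3.03. With t on 10 df, the smallest significant difference is about 6.75.
- If completers show 10 and the effect in non-completers is x, the effect in all participants is 0.58 × 10 + 0.42x. This is 7.9 at x = 5, 5.8 at x = 0 and 3.7 at x = −5.
- With the SE held fixed, a downward shift of (10 − 6.75) / 0.42 ≈ 7.7 points in intervention-arm non-completers alone removes significance. A shift of 10 / 0.42 ≈ 23.8 removes the whole effect.

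**4. What conditioning on baseline does and does not do**

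This is an illustrative simulation under assumed missingness models: true effect 10, SD 20, ICC 0.03, change falling 0.5 point per baseline point, and roughly 42% missing.

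| Missingness | Completer change score | Baseline-adjusted |
|---|---|---|
| Depends on baseline, opposite directions by arm (MAR) | 4.0 | 10.0 |
| Depends on unseen change, intervention arm only (MNAR) | 16.1 | 14.7 |

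The MAR case is severe. A shortfall of 6.0 at 0.5 per point means a baseline difference of about 12 points between the arms' completers. Under the same slope, each point of such imbalance costs 0.5 point. In the MNAR case, adjustment reduces the bias only from 6.1 to 4.7.

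**The case against.** A reader might infer that the trial will not deliver the intention-to-treat analysis it promises. The text does not support that. Units are analysed in the arm to which they were randomised, units with poor course adherence are kept, and staff may give follow-up data after their leader leaves the course. What the model omits is recruited participants with no month-7 score.

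It is also tempting to call the MAR condition backwards. Standard imputation is valid under MAR, so naming that assumption is conventional. The fault lies in using an unverifiable assumption as the trigger for imputing at all, with no alternative stated.

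A third inference would be that the harm comes from discarding 217 records and that restoring them cures it. With complete baseline data and one follow-up, baseline-only respondents add almost nothing to the treatment contrast. The gain comes from conditioning on baseline and on other predictors of response.

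Other points on the plan's side also stand:

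- The 58% is a planning allowance, and reminders and retention monitoring are described.
- The gaps of 5 and 10 points have no source in the documents.
- The imputation model and any tipping-point analysis may be in a statistical analysis plan that is not shown, so their absence here is not counted as an error.
- The general reference to participant characteristics might be stretched to cover baseline EBPQ. However, the background variables the protocol lists are age, gender, degrees, position and work experience.

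None of this rescues the rule as written, which fixes a completer change score and makes imputation optional on a condition that cannot be checked.

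**Conclusion.** The point holds as a missing-data weakness within an intention-to-treat analysis. The firm parts come from the protocol itself: about 42% expected missing, a change-score model that uses completers only, no listed baseline EBPQ covariate, and an imputation rule that cannot be applied as stated.

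The size and direction of any bias are not known. There is none if missingness is unrelated to change given arm and covariates, or if retention and completer/non-completer gaps match across arms. The range of 2.1 to 4.2 points (21% to 42% of the planned effect) rests on an assumed gap of 5 to 10 points in the intervention arm alone. It shows that the question matters and does not predict the result. The change should be made, but the point does not undermine the design.

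**What to change.** Delete the missing-at-random condition and name one primary approach that is applied whatever the missingness looks like, conditions on baseline EBPQ, and keeps unit as a random effect. Either of these would serve:

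- a baseline-constrained mixed model of baseline and month-7 EBPQ with random effects for unit and person, or a mixed model of the month-7 or change score adjusted for baseline EBPQ;
- multilevel multiple imputation by arm, using variables already collected at baseline (EBPQ, self-esteem, self-efficacy, implementation leadership, intention to leave, work experience).

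These are alternatives, not equivalents. The first uses EBPQ alone, while the second can draw on more predictors of response. Both assume MAR, and this should be stated as an assumption rather than tested as a precondition.

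Because neither removes MNAR bias, support the primary result with a delta-adjusted sensitivity analysis in which the shift for non-completers varies separately by arm. Report the shift at which the conclusion changes. If the statistical analysis plan already contains this, the protocol need only refer to it.

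The choice should be fixed before month-7 data are seen. The cost is some extra analysis work, with no new data and no change to recruitment.
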